### Participant Timeline

The participant timeline is summarized in Table 1, which outlines the schedule of enrollment, assigned care delivery, and outcome assessments over the 12-month study period. A schematic overview of the study stages and timing is provided in Figure 1.

### Sample Size

The sample size was determined for the primary outcome, change in SGRQ total score from baseline to 12 months, using a cluster randomized superiority design for 2 means (PASS, version 2021; NCSS LLC). We assumed a between-group difference (intervention minus control) in SGRQ change of 4 units (the minimal clinically important difference), a common SD of 10 units, an intracluster correlation coefficient of 0.01, an average cluster size of 15 participants per community-based primary care clinic, 80% power, and a 2-sided α of .05. Under these assumptions, 8 clinics per arm (16 in total) were required. Allowing for 20% loss to follow-up, we planned to recruit at least 10 clinics per arm.

Ultimately, 34 clinics (17 per arm) were enrolled, with a target of 15 participants per clinic (planned N=510). Assuming up to 20% attrition (≥408 analyzable participants, approximately 204 per arm), this sample provides >90% power to detect a 4‑unit difference even if the intracluster correlation coefficient increases to 0.03. Details of the sample size formulas and calculations are provided in Multimedia Appendix 1 (see methods 2).

### Data Collection and Management

Outcome, baseline, and other trial data will be collected at prespecified time points (Table 1). Data sources include hospital medical records and participant-reported questionnaires, administered in person at baseline and months 1, 6, 9, and 12, and by telephone at months 3, 7, and 10. Data will be recorded in an electronic case report form and stored in the EDC system by trained site pharmacists. EDC access will be role based and password protected.

Data quality will be promoted through standardized training on questionnaire administration and electronic case report form completion, the use of predefined variable definitions and built-in logic checks in the EDC system, and routine source data verification by an independent pharmacist at each site, supplemented by periodic central data monitoring and query resolution by the coordinating center. Standardized and validated instruments (SGRQ, TAI, and EQ-5D-5L) will be used as described earlier, and study-specific forms (pharmacy service survey) are provided in Table S4 in Multimedia Appendix 1.

To promote retention and complete follow-up, appointment reminders will be sent via the WeChat mini-program, and missed visits will be followed up by telephone. Participants who discontinue or deviate from the assigned care pathway will be encouraged to remain in the study for outcome assessment.

### Statistical Analysis

#### Baseline Characteristics

Baseline characteristics will be summarized by study arm using mean (SD) or median (IQR) for continuous variables and counts (%) for categorical variables. All statistical tests will be 2 sided, with a significance level of *P=*.05. Effect estimates will be reported with 95% CIs.

#### Analysis Populations

The primary analysis will follow the intention-to-treat principle, including all enrolled participants who provided informed consent, and analyzed according to the allocation of their recruiting clusters, regardless of intervention exposure or protocol deviations.

#### Primary Outcome Analysis

The primary end point (between-group difference in change from baseline to 12 months in SGRQ total score) will be analyzed using a linear mixed effects model accounting for clustering by site and adjusting for baseline SGRQ, cluster effects, and prespecified baseline characteristics. Treatment effect will be expressed as the adjusted between-group difference in change.

#### Secondary and Other Outcome Analysis

Continuous secondary outcomes (eg, TAI-10 and EQ-5D-5L utility index) will be analyzed using linear mixed effects models, adjusting for baseline value and cluster effects. Results of the pharmacy service survey will be summarized using descriptive statistics (proportions).

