**Objective:**

The primary objective is to compare the change in HRQoL, measured using the St George’s Respiratory Questionnaire, between the intervention and control groups from baseline to 12 months. Secondary objectives are to assess changes in medication adherence (Test of Adherence to Inhalers), quality of life (EQ-5D-5L), COPD-related medical costs, and patient-reported pharmacy service experience.

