**Methods:**

This 1-year cluster randomized controlled trial evaluates a multifaceted pharmaceutical care intervention in adults with moderate to very severe COPD (Global Initiative for Chronic Obstructive Lung Disease, stages 2-4) who have confirmed suboptimal inhaler practice but remain matched to an appropriate inhaler device based on peak inspiratory flow rate measured using a digital tool. In total, 34 hospital-based cough and wheeze pharmaceutical care clinics were recruited and randomized (1:1) to either an intervention or a control group. The target sample size is 15 patients per site. Participants in the intervention group will receive tailored support using electronic adherence monitoring, inhaler use technique assessments, and peak inspiratory flow rate to optimize device selection and self-management. Participants in the control group will receive usual pharmaceutical care. Descriptive statistics will be used to summarize participant characteristics and outcomes. Linear mixed effects models will be used to compare primary and secondary outcomes. Subgroup analyses will explore effects by age, sex, education level, place of residence, and smoking status. Pharmacy service survey data will be analyzed qualitatively.

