##### Pharmacy Service Survey

A pharmacy service survey will be used to assess patients’ perceived improvements in COPD-related and medication-related knowledge, self-reported quality of life, mastery of correct inhaler use after participation, and adequacy of communication with pharmacists (Table S4 in Multimedia Appendix 1). This survey will be administered at month 12 (Table 1).

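### The pharmacy service survey is listed among outcomes assessed for change, but it is given once at month 12 and only described, so the plan yields no measured change and no between-arm estimate.

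*Protocol article*

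**What the plan says.** - **Objective.** In the Abstract of the protocol article, the statement of secondary aims reads: "objectives are to assess changes in medication adherence (Test of Adherence to Inhalers), quality of life (EQ-5D-5L), COPD-related medical costs, and patient-reported pharmacy service experience".
- **Timing.** The Pharmacy Service Survey section says: "This survey will be administered at month 12". Table 1 agrees, with a single tick in the month-12 column.
- **Content.** The same section says that the survey covers perceived improvement in knowledge, self-reported quality of life, mastery of the inhaler after participation, and adequacy of communication with pharmacists. The items themselves are in Table S4, which is not shown.
- **Analysis, main text.** Secondary and Other Outcome Analysis: "Results of the pharmacy service survey will be summarized using descriptive statistics (proportions"). The mixed model in that section is for continuous outcomes and adjusts for a baseline value.
- **Analysis, Abstract.** "Pharmacy service survey data will be analyzed qualitatively".
- **Status.** The survey sits under Secondary Outcomes. Strengths and Limitations includes it in the group it calls primary and key secondary, and warns that these patient-reported outcomes are open to performance and reporting bias.

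**The concern.** The objective, the schedule and the analysis of this outcome do not fit together. A change needs two measurements, and there is one. A randomized comparison needs a contrast between arms, and none is stated. The two descriptions of the analysis also differ, since proportions are quantitative.

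Both arms have pharmacist visits at baseline and months 1, 6 and 9, and both receive inhaler training. Favourable answers to questions about perceived improvement are therefore plausible in either arm. Proportions alone would not show how much of a favourable result belongs to the programme and how much to a year of contact with any pharmacist. The randomized contrast at month 12 is the part of the data that addresses this, and the plan leaves it unused for an outcome it ranks as key secondary.

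**Working it through.** **1. The texts side by side**

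| Outcome | Measured | Defined as | Planned analysis |
|---|---|---|---|
| TAI-10 | baseline, months 1, 6, 9, 12 | between-group difference in change to month 12 | mixed model with baseline value and cluster |
| EQ-5D-5L | baseline, month 12 | between-group difference in change to month 12 | mixed model with baseline value and cluster |
| Pharmacy service survey | month 12 | no contrast defined | proportions (main text); qualitative (Abstract) |

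The survey has one measurement per participant, so no change score can be formed. No between-arm estimate is planned for it. The statement under Baseline Characteristics that effect estimates carry 95% CIs therefore has nothing to act on here.

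**2. Would a month-12 contrast be informative?**

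The protocol gives no figure for the survey. Its Sample Size section, from which two inputs are borrowed below, does reproduce for the primary outcome: 99 per arm for a 4-unit difference with SD 10; design effect 1 + (15 − 1) × 0.01 = 1.14; 99 × 1.14 = 112.9; 112.9 / 15 = 7.52, rounded up to 8 clinics per arm.

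Inputs for the survey:
- 454 enrolled (Results) in 34 clinics.
- 20% loss. This is the Sample Size allowance, and its use for survey response is an assumption.
- Intracluster correlation (ICC) 0.01 and 0.03. These are the Sample Size values for the SGRQ, and their use for the survey is an assumption.
- Proportion p of 0.5 (widest interval) and 0.9 (mostly favourable answers). Both are assumptions.

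Steps:
- Respondents per arm: 454 × 0.8 / 2 = 181.6, about 182. Per clinic: 454 × 0.8 / 34 = 10.7.
- Design effect (DE): 1 + (10.7 − 1) × 0.01 = 1.097; 1 + (10.7 − 1) × 0.03 = 1.29.
- Half-width of the 95% CI for a difference: 1.96 × sqrt(2 × p(1 − p) / 182 × DE).

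| p | ICC 0.01 | ICC 0.03 |
|---|---|---|
| 0.5 | 10.8 points | 11.7 points |
| 0.9 | 6.5 points | 7.0 points |

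With the planned 204 per arm (12 per clinic), the half-widths at p = 0.5 are 10.2 and 11.2 points. On the same basis, power to separate 60% from 75% is about 87% at ICC 0.01 and 80% at ICC 0.03. The contrast is feasible with data already scheduled.

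**The case against.** The strongest reply is that this is loose wording in an Abstract and not a flawed analysis. Several parts of it stand.

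- **The word for change is shorthand.** Costs are in the same Abstract list, yet the Medical Cost section defines them as a 12-month cumulative total. The main text defines a change for TAI-10 and EQ-5D-5L and does not for the survey.
- **Perceived improvement needs no baseline.** A reader might infer that the survey says nothing about change. That goes too far: patients can report, looking back, whether they feel they improved. What is missing is a measured change.
- **The analysis is not stated three ways.** The Abstract also says: "Linear mixed effects models will be used to compare primary and secondary outcomes". A reader might count this as a third account, but it is a general sentence. The same paragraph gives the survey its own sentence, and the main text limits mixed models to continuous outcomes. The conflict is between two accounts.
- **Description is a legitimate choice for a study-specific form.** No section plans an efficacy claim from it. That readers would credit the programme with high proportions is a prediction, not something the protocol says.
- **The items are not visible.** Without Table S4 the response scale is unknown, so one fixed model for every item cannot be prescribed.

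Two parts do not stand. The main text does not defer the analysis to a later plan; it fixes it as descriptive. And an outcome ranked as key secondary in a randomized trial is better served by a contrast with an interval than by bare proportions, when the data for it are already scheduled.

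**Conclusion.** The point holds as a minor one. As written, the survey can describe perceived improvement at month 12. It gives no measured change from baseline and no between-arm estimate, and the Abstract and main text disagree on how it will be analyzed.

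The lack of a between-arm estimate comes from the planned analysis. A reader might infer that the design rules it out, but the common schedule in Table 1 implies that both arms are surveyed. A reader might also infer that any difference under about 10 points is compatible with no effect. That holds only for proportions near 50%; at 90% the half-width is about 6.5 to 7 points.

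The precision figures assume 182 respondents per arm and an ICC carried over from the SGRQ, and serve as illustration. The inconsistency itself rests on the text and needs no figures. The primary end point and the TAI-10 and EQ-5D-5L analyses are unaffected.

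**What to change.** 1. **Abstract, Objective:** take the survey out of the list governed by change and state it as pharmacy service experience at month 12, compared between groups.
2. **Secondary and Other Outcome Analysis:** keep the proportions, give them by arm, and add a between-arm difference with a 95% CI that accounts for clustering by hospital. Choose the model to fit the response scale in Table S4. Label these estimates exploratory, with no multiplicity claim.
3. **Abstract, Methods:** reconcile the statement that the survey is analyzed qualitatively with the proportions in the main text. If Table S4 has open-text items, say that the qualitative analysis applies to those.

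The cost is a few lines of text and code, with no new data. By 31 December 2025 only 16 of 454 participants had completed the 12-month follow-up, so the change can be made and dated before most of the survey data exist. The downside is several exploratory estimates from a self-report survey in participants who cannot be fully masked. The contrast does not remove the reporting bias that the protocol acknowledges, and the report should say so.

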#### Subgroup Analyses

Subgroup analyses for the primary outcome will be conducted based on the following variables: age (<65 vs ≥65 years), sex (male vs female), education level (high school or below vs college or university or above), place of residence (rural vs urban), COPD severity (moderate vs severe vs very severe), smoking status (current or former smoker vs never smoker), and baseline number of acute exacerbations of COPD (0 vs ≥1). Interaction terms for group and these covariates will be included in the analysis.

#### Missing Data and Sensitivity Analyses

In the primary analysis, missing data for the primary outcome (SGRQ) will be handled using the last observation carried forward method. To assess the robustness of the primary outcome to different assumptions about missing data and analysis populations, several sensitivity analyses will be conducted, including (1) reanalysis of the primary outcome in the per‑protocol population, (2) complete‑case analysis without imputation, and (3) multiple imputation for missing SGRQ data.

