**Exclusion criteria**
Inability to obtain informed consent from the patient or family membersComorbidities precluding participation, including terminal illness (life expectancy <6 months), active tuberculosis or lung cancer, or cognitive or physical impairment affecting inhaler usePregnancy or lactationConcurrent enrollment in other clinical trialsInability to complete the 12-month follow-up (eg, relocation plans)Other conditions in which the pharmacist who evaluated the participant is unable to comply with the trial

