### Study Outcomes

#### Primary Outcome

The St George’s Respiratory Questionnaire (SGRQ) will be used to assess HRQoL. The primary end point is the between-group difference in change from baseline to 12 months in the SGRQ total score, measured at baseline and 12 months after initiation of the intervention. The SGRQ was originally developed by Jones et al [29] and consists of 50 items divided into 3 sections: symptoms, activities, and impact. The scoring range is from 0 to 100, with a lower score indicating better health status in patients with COPD. SGRQ will be administered at baseline and at months 1, 6, 9, and 12 (Table 1).

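### Last observation carried forward as the primary method for missing 12-month SGRQ can bias the month-12 difference in either direction and understate its uncertainty

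*Protocol article*

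**What the plan says.** The Primary Outcome section defines the end point as the "between-group difference in change from baseline to 12 months in the SGRQ total score". It also states that "SGRQ will be administered at baseline and at months 1, 6, 9, and 12", and Table 1 agrees. Under Primary Outcome Analysis, the end point "will be analyzed using a linear mixed effects model accounting for clustering by site and adjusting for baseline SGRQ". That section does not say whether the month 1, 6 and 9 scores enter the model. The intention-to-treat set is described as "including all enrolled participants who provided informed consent", so participants without a month-12 score must be handled somehow.

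The section Missing Data and Sensitivity Analyses fixes how: "missing data for the primary outcome (SGRQ) will be handled using the last observation carried forward method". It gives no reason for the choice. Three sensitivity analyses follow: per protocol, complete case and multiple imputation. The Sample Size section quantifies the expected loss ("Assuming up to 20% attrition"), leaving at least 408 analyzable participants of a planned 510.

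**The concern.** Carrying forward replaces a missing month-12 score by the score from month 9, 6, 1 or even baseline. That is right only if the participant's score would not have changed after that visit. The method is not generally valid under missing at random. It is not valid even under completely random dropout when mean scores change over time, and change over time is what the trial hopes to produce. It also counts each filled-in value as a real measurement, so the precision claimed for the month-12 difference exceeds what the observed month-12 data support.

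At stake are the headline estimate, its confidence interval and its P value. Unequal dropout is plausible: visits last about 30 minutes in one arm and about 10 in the other, only one arm has the digital sensor support, and the article concedes that participants cannot be fully blinded.

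**Working it through.** **Inputs from the Sample Size section.** Difference 4, SD 10, ICC 0.01 (checked up to 0.03), 15 participants per clinic, 17 clinics per arm, planned N = 510, up to 20% attrition, two-sided α of 0.05.

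**Assumptions not in the document.** The SGRQ trajectories, the dropout split between arms, and the timing of dropout. Unless stated otherwise, last visits are spread evenly over baseline and months 1, 6 and 9.

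**1. The plan's own figures.**
- Per arm without clustering: 2 × 10² × (1.960 + 0.842)² / 4² = 98.1.
- Design effect: 1 + 14 × 0.01 = 1.14. Then 98.1 × 1.14 = 111.8, and 111.8 / 15 = 7.46, so 8 clinics per arm. 8 / 0.8 = 10.
- With 408 analyzable (12 per clinic) and ICC 0.03, power is 0.939 by the normal approximation and about 0.92 by the noncentral t with 32 degrees of freedom.

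Both statements in the plan reproduce (8 clinics per arm, and more than 90% power).

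**2. Expected carried-forward estimate when there is an effect.** With dropout proportion p, the estimate is (1 − p) × (effect at month 12) + p × (mean effect at the last visit).
- *Linear build to -4.* Mean effect at the last visit: -4 × (0 + 1 + 6 + 9) / (4 × 12) = -1.33. Estimate: 0.8 × (-4) + 0.2 × (-1.33) = -3.47.
- *Same effect, baseline carried for every dropout.* 0.8 × (-4) + 0 = -3.20.
- *Immediate, constant effect of -4.* Mean effect at the last visit: (0 + 3 × (-4)) / 4 = -3. Estimate: 0.8 × (-4) + 0.2 × (-3) = -3.80.

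**3. No true effect, unequal dropout.** Both arms worsen linearly by 4, so the mean carried change is 1.33.
- Intervention, 25% dropout: 0.75 × 4 + 0.25 × 1.33 = 3.33.
- Control, 15% dropout: 0.85 × 4 + 0.15 × 1.33 = 3.60.
- Difference: -0.27, a spurious benefit. If both arms instead improve, the sign reverses.
- With equal dropout and equal trajectories, or with flat trajectories, the difference is 0.

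**4. Standard error at ICC 0.03.**
- 510 treated as observed (255 per arm, 15 per clinic): √(2 × 100 × 1.42 / 255) = 1.055.
- 408 observed (204 per arm, 12 per clinic): √(2 × 100 × 1.33 / 204) = 1.142.
- Ratio: 0.92, about 8% smaller.

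**5. Power (noncentral t, 32 degrees of freedom).**

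| Case | Difference | SE | Power |
|---|---|---|---|
| 408 observed, unbiased | 4.00 | 1.142 | 0.92 |
| Carried forward, linear build | 3.47 | 1.055 | 0.89 |
| Carried forward, baseline for all dropouts | 3.20 | 1.055 | 0.84 |

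**6. Simulation.** 1,000 runs; 34 clinics of 15; ICC 0.03; an effect building to -4; 20% dropout completely at random. Visit correlations (0.5 to 0.7) and visit SDs (7 to 10) were assumed. The repeated-measures fit used the known covariance.
- Carried forward: mean -3.51, 95% CI coverage 0.917, power 0.919.
- Repeated-measures model on all visits: mean -3.97, coverage 0.956, power 0.947.

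**The case against.** **The size is modest and rests on assumptions.** This stands. Attrition of 20% is a planning ceiling, and the protocol plans reminders, telephone follow-up of missed visits and continued assessment after discontinuation. At 10% dropout the bias in the linear case halves, from 0.53 to 0.27 units. The spurious -0.27 is about a quarter of a standard error and would raise two-sided type I error only to about 0.057.

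**The sensitivity analyses would probably reveal a material distortion.** They might, but the prespecified conclusion would still be the carried-forward one.

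Stronger readings are tempting but not supported:

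- *The estimate is certainly biased.* With no effect and equal dropout and trajectories the bias is zero.
- *The standard error is wrong for the estimator.* In the simulation it matched the estimator's own sampling spread (1.00 against 1.00 with no effect and equal dropout), and type I error was not inflated with equal dropout. It is too small only as a statement of uncertainty about the true month-12 effect.
- *Power falls to 84%, or to 78% if baseline is carried.* Those figures pair the attenuated effect with the standard error for 408 participants, whereas carrying forward analyses all 510.
- *Deaths are foreseeable because the only relevant exclusion is "terminal illness (life expectancy <6 months".* The criteria also exclude active tuberculosis, lung cancer and people unable to complete the 12 months, and no death rate is given. A likelihood model under missing at random also implies month-12 values after death, so changing the method does not by itself settle that question.
- *The intermediate scores serve only to be carried forward.* The article does not say which visits enter the model, and nothing bars those scores from the multiple imputation.

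**Conclusion.** The concern holds in a limited form. The protocol itself fixes the method and gives no reason for it. For an end point defined at month 12, carrying forward can shift the estimate in either direction and makes the uncertainty about the month-12 effect look smaller than it is.

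In the scenarios worked by formula with a true -4 effect and 20% dropout, the attenuation is 0.2 to 0.8 units. The unequal-dropout scenario without an effect gives 0.27 units. The standard error is about 8% smaller than 408 observed values would give at ICC 0.03. Power falls from about 92% to about 89% in the linear case, and to about 84% if baseline is carried for every dropout. The standard errors and powers use the planned 510; 454 were enrolled. The true direction and size cannot be known from the document. The change is still worth making, because a better-founded method needs no further data.

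**What to change.** Before unblinding, replace the primary handling of missing SGRQ by one of two options:

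1. A likelihood-based repeated-measures mixed model of SGRQ at months 1, 6, 9 and 12, with arm, visit, arm-by-visit interaction, baseline SGRQ, a random site effect and within-participant correlation. The month-12 contrast is the primary estimate.
2. Multiple imputation that respects clustering and uses the intermediate visits. This promotes an analysis that the protocol already lists.

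In either case, add a delta-adjusted sensitivity analysis for data missing not at random. Report deaths by arm and state how they are handled. Drop carrying forward, or keep it only as a sensitivity analysis.

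The cost is revised wording and slightly more programming; no new data or participants are needed. Both options rely on missing at random, which the sensitivity analyses probe. At the last report 16 of 454 participants had completed the 12-month follow-up, so the change can still be made without knowledge of the results.
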